### Data analysis

2.8

All quantitative analyses will be conducted using recognized statistical software packages, including SPSS, Jamovi or R. Prior to carrying out the main analyses, the dataset will undergo systematic cleaning procedures to ensure accuracy and completeness. This process will include the identification of missing or inconsistent responses, the examination of outliers and the verification of the logical coherence of participants' data across time points. When suitable, missing data will be handled using established statistical approaches suitable for longitudinal trials, such as multiple imputation or mixed-effects modeling, in accordance with current methodological recommendations. The primary endpoint for between-group comparisons is the post-intervention assessment (T1). The 6-month follow-up (T2) is intended to evaluate the maintenance of treatment effects within the intervention group only; therefore, no between-group comparisons will be conducted at T2. To account for the repeated-measures structure of the data and the correlation among observations across time, analyses will be carried out using mixed-effects models or repeated-measures analysis of variance, depending on the distributional properties of the data. These models will allow the estimation of both within-participant changes over time and between-group differences, while accommodating incomplete data without necessitating case wise deletion. Effect sizes and confidence intervals will be reported to quantify the magnitude and precision of observed differences.

Associations among variables of interest will be explored using multivariate techniques. To better understand the mechanisms underlying treatment effectiveness, mediation analyses will be conducted to examine whether changes in PF or related processes account for improvements in pain acceptance or other clinical outcomes. Moderation analyses will also be performed to identify potential participant-level characteristics that may influence the direction or magnitude of treatment effects.

All analyses will be performed under the intention-to-treat principle whenever feasible, ensuring that participants are analyzed within their originally assigned groups regardless of treatment adherence. Sensitivity analyses will be conducted to evaluate the robustness of the findings under different assumptions regarding missing data handling (e.g., complete-case vs. imputed datasets), model specifications, and adjustment for relevant baseline covariates.

Qualitative data from the clinical interviews will be analyzed using reflexive thematic analysis in accordance with Braun and Clarke's framework (Braun and Clarke, 2006). A primarily inductive analytic approach will be adopted to allow themes to emerge from participants' narratives while remaining sensitive to ACT-related and digital-intervention processes. Data collection will continue until thematic saturation is reached, defined as the point at which no substantially new themes relevant to the research questions are identified in consecutive interviews. Rigor and trustworthiness will be supported through independent coding of a subset of transcripts by at least two researchers, regular analytic discussions, reflexive memoing, documentation of coding decisions in an audit trail and reporting guided by relevant qualitative reporting standards such as COREQ (Tong et al., 2007).

The economic evaluation will be integrated with the clinical data and will rely on the calculation of Quality-Adjusted Life Years (QALYs) derived from EQ-5D-3L utility scores. Incremental cost-effectiveness ratios will be estimated by comparing the costs and outcomes associated with MobACT relative to the waitlist condition, adopting both healthcare-sector and societal perspectives. The uncertainty surrounding these estimates will be examined through non-parametric bootstrapping procedures and appropriate graphical representations, such as cost-effectiveness planes and acceptability curves. The trial protocol and statistical analysis plan will be made publicly accessible through the ClinicalTrial.gov registry (NCT07270588).

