### Study design

2.1

This study is a multicenter two-arm, parallel-group randomized controlled trial (RCT) coordinated by the Department of Psychology, Università Cattolica del Sacro Cuore, Milan, Italy, with collaborating sites at the Università degli Studi di Verona, Verona, Italy, and Alma Mater Studiorum—Università di Bologna, Bologna, Italy, and conducted in collaboration with Linköping University, Linköping, Sweden, and Uppsala University, Uppsala, Sweden.

Participants will be randomized in a 1:1 ratio to either immediate access to MobACT or to a waitlist control condition. Participants allocated to the waitlist control condition will complete the baseline (T0) and post-intervention (T1) assessments without access to MobACT and will receive access to the programme only after completion of T1, following the primary between-group comparison. Because of this delayed-intervention design, valid between-group comparisons are restricted to T1. The 6-month follow-up (T2) will be conducted in the intervention group only to evaluate maintenance of treatment effects. Informed consent will be obtained from all participants before any study-related procedures are conducted (Figure 1 presents the study flow diagram).

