### Sample size calculation

2.3

The required sample size was determined using G^*^Power software (version 3.1.9.7) for an F test (ANOVA: repeated measures, within-between interaction), with the following parameters: effect size f = 0.15, alpha = 0.05, power (1-beta) = 0.95, two groups, repeated measurements, correlation among repeated measures = 0.50 and no sphericity correction for the primary two-time-point contrast. The assumed effect size was deliberately conservative. Although psychological and online ACT interventions for chronic pain often produce small-to-moderate or moderate effects on pain acceptance and pain interference (Buhrman et al., 2013; Lin et al., 2017; Trompetter et al., 2015; Vugts et al., 2018; van de Graaf et al., 2021; Vlaescu et al., 2016), a smaller effect was selected to avoid overestimating treatment effects in the first formal evaluation of an Italian internet-based ACT programme for CP and in a heterogeneous, fully online recruited sample. The analysis indicated a required total sample size of *N* = 116.

To account for potential attrition, the planned sample size has been increased to 140 participants. This inflation allows approximately 17% attrition while retaining an analyzable sample close to *N* = 116. The assumption is broadly consistent with attrition observed in the Swedish guided internet-delivered ACT trial on which MobACT is based, in which 15 of 76 randomized participants (19.7%) did not provide post-treatment data (Buhrman et al., 2013). Automated reminders, weekly notifications and the availability of therapist contact through the platform are expected to support retention in the present trial.

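### Read together, the sizing test and the analysis text make the primary comparison a difference in CPAQ change scores; adjusting T1 CPAQ for T0 CPAQ would cut its variance by 25% at the protocol's own correlation, with no new data.

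*Protocol article*

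**What the plan says.** Section 2.3 (Sample size calculation) obtains the sample size "for an F test (ANOVA: repeated measures, within-between interaction"), with "effect size f = 0.15, alpha = 0.05, power (1-beta) = 0.95, two groups" and "correlation among repeated measures = 0.50 and no sphericity correction for the primary two-time-point contrast". The result is a "required total sample size of *N* = 116", raised to 140 randomised for attrition.

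Section 2.8 (Data analysis) makes T1 the endpoint for between-group comparison. It plans mixed-effects models or repeated-measures ANOVA, chosen according to the distribution of the data, and says of them: "These models will allow the estimation of both within-participant changes over time and between-group differences". It names no covariate for these models and does not say which model term is the primary test. Baseline adjustment appears once, in the list of sensitivity analyses: "model specifications, and adjustment for relevant baseline covariates". The covariates are not named.

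Section 2.4 (Procedure) places randomisation after the baseline assessment, so T0 CPAQ exists for everyone randomised. Sections 1.1 and 2.1 restrict T2 to the intervention arm.

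**The concern.** With two time points and complete data, the group-by-time term in a repeated-measures ANOVA, or in a mixed model with freely estimated baseline means, is the between-arm difference in mean change. It subtracts the whole of the baseline score, which fixes the baseline coefficient at 1. With equal SDs at T0 and T1, the protocol's correlation of 0.50 implies a coefficient of about 0.5. The change score therefore over-corrects any chance baseline difference and carries avoidable noise. Because baseline is measured before randomisation, the arms have equal expected baselines, and the change-score contrast makes no use of that fact.

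At stake is precision on the primary outcome: a wider confidence interval and lower power than the same participants could give.

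**Working it through.** **Inputs from the protocol.** f = 0.15, alpha = 0.05, two groups, correlation rho = 0.50, target power 0.95, stated N = 116, and a two-time-point contrast (section 2.3); 1:1 allocation (section 2.1). The number of measurements m entered in the software is not stated. I also assume equal SDs at T0 and T1 and a linear relation between them.

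**Step 1: the plan's own figure.** For the within-between interaction in the software's default form, lambda = f²·N·m/(1 − rho), with df1 = (k − 1)(m − 1), df2 = (N − k)(m − 1) and k = 2 groups.
- m = 2, N = 116: lambda = 0.0225 × 116 × 2 / 0.50 = 10.44; power 89.3%. The N needed for 95% is 147 (148 with equal arms).
- m = 3, N = 116: lambda = 0.0225 × 116 × 3 / 0.50 = 15.66; power 95.0%.

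So 116 is reproduced with three measurements and not with the two that the contrast uses.

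**Step 2: effect in SD units.** With two groups and two times, f = 0.15 corresponds to a difference in mean change of d = 4f = 0.60 SD.

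**Step 3: variances.** With total N split equally and outcome variance σ²:
- change score: 4·2(1 − rho)σ²/N, which is 4 × 1.00σ²/N at rho = 0.50;
- T1 adjusted for T0: 4(1 − rho²)σ²/N, which is 4 × 0.75σ²/N at rho = 0.50.

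The ratio is (1 + rho)/2 = 0.75, so the cut is (1 − rho)/2 = 25%. As 1/0.75 = 1.33, this is worth about a third more participants.

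**Step 4: power at N = 116 and d = 0.60.**
- Change score: lambda = 0.36 × 116/4 / 1.00 = 10.44, 114 df; power 89.3%.
- Adjusted: lambda = 0.36 × 116/4 / 0.75 = 13.92, 113 df; power 95.9%.

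A simulation of 40,000 trials gave 89.5% and 95.6%, with a variance ratio of 0.76. The adjusted analysis needs N = 111 for 95% (112 with equal arms).

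**Step 5: attrition as in the Swedish trial cited in section 2.3.** 140 × (1 − 15/76) = 112.4, so about 112 analysed: 88.2% for the change score and 95.3% adjusted.

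**Step 6: dependence on rho (N = 116, d = 0.60).**

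| rho | Variance cut | Change score | Adjusted |
|---|---|---|---|
| 0.3 | 35% | 77.3% | 91.9% |
| 0.4 | 30% | 83.3% | 93.8% |
| 0.5 | 25% | 89.3% | 95.9% |
| 0.6 | 20% | 94.8% | 98.0% |
| 0.7 | 15% | 98.5% | 99.4% |

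The adjusted analysis reaches 95% at N = 116 from rho of about 0.46; the change score does so from about 0.61.

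**Step 7: dependence on the effect (N = 116, rho = 0.50).** The smaller effects are my assumptions, to show the range. At 0.50 SD the powers are 76.1% (change score) and 86.9% (adjusted); at 0.40 SD they are 57.0% and 69.4%.

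**The case against.** The strongest reply is that section 2.8 fixes very little. It never calls the interaction the primary test. A T0–T1 mixed model with a common baseline mean would fit its wording and would have about the efficiency of ANCOVA. The mean structure and covariates are ordinary SAP content, and the SAP is not shown. This stands in part: that the primary test is the interaction is an inference, and a reader should not take it as stated. The inference is still the natural one. Section 2.3 ties its interaction test to the primary two-time-point contrast, repeated-measures ANOVA (one of the two named options) cannot impose a common baseline, and the only mention of baseline adjustment is as a sensitivity analysis. An SAP written faithfully to this text would inherit the change-score comparison.

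Three stronger readings are tempting, and the documents do not support them.
- *Adjustment for baseline CPAQ has been relegated to a sensitivity analysis.* The phrase in section 2.8 does not name CPAQ and may mean other variables. What can be said is that nothing places baseline CPAQ in the primary model as a covariate.
- *Adjustment guarantees the stated 95% power.* It does so at N = 116 only if rho is about 0.46 or more and the effect is 0.60 SD. The article gives no evidence for rho = 0.50.
- *The planned test is invalid.* Under randomisation it is unbiased with correct type I error. Sensitivity to a chance baseline imbalance affects precision and the estimate conditional on that imbalance, not validity.

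It is also fair to say that the gap between 89.3% and 95% at N = 116 is a separate sample-size error. The case for adjustment does not need it, because the adjusted analysis is the more precise at every rho below 1.

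**Conclusion.** The point holds as one of precision. On the most natural reading, the planned primary comparison is a difference in change scores. Baseline adjustment would lower its variance by (1 − rho)/2, which is 25% at the protocol's correlation, and raise power from 89.3% to 95.9% at N = 116 and 0.60 SD. Over rho from 0.3 to 0.7 the gain shrinks from 14.6 percentage points (77.3% to 91.9%) to 0.9 (98.5% to 99.4%). The figures rest on equal SDs at T0 and T1, a linear relation and the 0.60 SD effect. This is worth changing, but the trial would still give a valid answer without it.

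**What to change.** Before outcome data are examined:

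1. Specify as primary the between-arm difference in T1 CPAQ adjusted for T0 CPAQ, either by ANCOVA or by a mixed model on T0 and T1 with baseline means constrained equal across arms. The mixed model keeps participants who miss T1.
2. Use the same form for each continuous secondary outcome, with its own baseline value.
3. Restate the power in section 2.3 on that model, showing how it varies with rho and with the assumed 0.60 SD effect.
4. Correct the N = 116 calculation separately, because it corresponds to three measurements and not to the two-time-point contrast.

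The cost is one degree of freedom and no new data. Because the trial has started (section 4), the change should be dated and justified in the protocol, the SAP and the registry. If it counts as a substantial amendment, it also needs the ethics committee approval described in section 7.

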## Expected results

3

Over the past 10 years, ICBT has been developed and tested in several controlled studies, and more recently, multiple studies have implemented Internet-delivered interventions based on ACT principles (Bendelin et al., 2020; Buhrman et al., 2013; Lin et al., 2017; Trompetter et al., 2015). This therapeutic approach, due to its characteristics, may be particularly useful in supporting patients with CP. Hughes, Clark (Hughes et al., 2017) and Veehof, Trompetter (Veehof et al., 2016) emphasize that ACT-based treatments effectively reduce pain intensity, pain interference and emotional distress, while improving patients' QoL.

It is hypothesized that, compared with the waitlist control condition, MobACT will improve pain acceptance at T1 and will produce favorable changes in clinically relevant secondary outcomes, including pain interference, pain intensity, quality of life, sleep quality, psychological flexibility, self-efficacy, coping, anxiety and depressive symptoms. It is also expected that changes in ACT-related processes, particularly psychological flexibility and pain acceptance, will help explain improvements in clinical outcomes, and that the intervention will show a favorable cost-effectiveness profile over the T0–T1 comparison period.

## Strengths and limitations

4

This study presents several methodological strengths. First, it is a randomized controlled trial evaluating a guided internet-based ACT intervention for adults with chronic pain in Italy, a context in which no internet-delivered ACT programme for CP has yet been formally tested. The intervention is delivered through the secure and evidence-based *Iterapi* platform, which has been widely used for digital mental health interventions and supports standardized treatment delivery. In addition, the study includes a comprehensive assessment of clinical, psychological and economic outcomes, allowing for a multidimensional evaluation of intervention effects, including cost-effectiveness. The use of validated Italian versions of primary and secondary outcome measures further strengthens the methodological rigor and cultural appropriateness of the assessment strategy. However, some limitations should be acknowledged. The waitlist control condition is a relatively weak comparator and does not control for all non-specific factors such as expectancy, therapist contact or digital attention. The delayed-intervention design restricts valid between-group comparisons to the post-intervention assessment (T1), because waitlist participants receive access to MobACT after T1; consequently, no causal between-group inference can be made regarding 6-month maintenance effects. Participants and clinicians cannot be blinded to allocation, and all outcomes are self-reported and administered online, which may introduce expectancy effects, response bias and variability related to pain intensity, emotional state or cognitive load at the time of questionnaire completion. Recruitment conducted entirely online may also limit representativeness by favoring individuals with higher digital literacy, greater motivation for psychological intervention or better access to internet-enabled devices. Finally, because publication of this protocol occurs after trial initiation, the protocol should be interpreted together with the trial registry and ethics documentation; nevertheless, the present manuscript reports no outcome data and clarifies the pre-specified design, outcome hierarchy and analysis plan before trial results are disseminated.

## Data protection and confidentiality

5

All data collected during the study will be managed in line with the General Data Protection Regulation (GDPR, EU Regulation 2016/679). Data will be stored on encrypted servers through the secure *Iterapi* platform. Personal identifiers will remain strictly separated from all clinical and research data and will be linked only through anonymized participant codes (e.g., 1248cgyy, 1307tzhf). Access to the data will be restricted to authorized members of the research team. Following completion of the trial, data will be retained for a minimum of five years, in accordance with institutional and national guidelines.

## Data monitoring

6

Throughout the trial, regular internal meetings will be held every three weeks to review recruitment progress, adherence levels, technical aspects of data acquisition and any issues arising during implementation. Deviations from the protocol, if any, will be documented, evaluated and reported according to ethical requirements and best practices for clinical research transparency. Moreover, the *Iterapi* platform automatically records all participant activity, including module access, questionnaire completion and timestamps for each assessment. These built-in monitoring functions allow the research team to identify irregularities, missing data or technical issues in real time. Any inconsistencies or interruptions in the data collection flow will be reviewed by the investigators, who will take appropriate action to ensure continuity and accuracy in data collection.

## Protocol amendments

7

No substantive changes to the approved study design, intervention, eligibility criteria, outcome hierarchy, assessment schedule or primary endpoint have been introduced as part of the peer-review revision of this protocol manuscript. Any future substantial amendments that may influence participant safety, trial conduct or scientific integrity will be submitted to the Ethics Committee of Universit0 Cattolica del Sacro Cuore, Milan, for approval before implementation. All approved changes and registry clarifications will be documented on ClinicalTrials.gov with the appropriate date and rationale. The present manuscript reflects the protocol version currently approved by the Ethics Committee and registered on ClinicalTrials.gov.

## Interim analysis and stopping guidelines

8

No interim analyses are planned for this trial, given the low-risk nature of the study. Therefore, no formal stopping guidelines have been established. Nevertheless, the study team will continue to monitor participants' safety throughout the trial, and the intervention delivery may be paused in the case of adverse psychological events.

## Protocol adherence and reporting guidelines

9

This protocol was developed and reported in accordance with the SPIRIT 2013 guidelines and their 2025 update (Chan et al., 2025). A completed SPIRIT 2025 checklist is provided as supplementary material (see Supplementary file 2).

## Dissemination plan

10

Study findings will be disseminated via publications in open-access, peer-reviewed journals and presentations at national and international conferences in the fields of health psychology, pain medicine and digital health. Results will be also communicated to patient organizations (particularly the ones involved in study recruitment) and clinical partners using summary reports. To facilitate broader dissemination, lay summaries will be developed for the public and patient communities, including dissemination through social media. Where appropriate, anonymized datasets and statistical analysis code will be made available to researchers upon reasonable request.
